#### Musculoskeletal pain

Musculoskeletal pain from the head, neck, shoulders, thoracic spine, lumbar back, hips, knees, and feet during the past 3 months will be measured at baseline and at the 2-, 6-, 10-, and 13-month follow-up visits using the Chronic Pain Grade Questionnaire (CPGS) [28]. Participants will complete the questionnaire at home. The CPGS has been shown to be a valid questionnaire [28, 29], and includes subscales for both pain severity and pain-related disability. The subscale scores are combined into a grade, classifying the participants into 5 categories ranging between 0 (no pain problem) to 4 (severe interference). An additional question was recently added to the questionnaire, which asks for the number of days of pain during the past 6 months. Pain is also classified as non-persistent (1–89 pain days) or persistent (90–180 pain-days) [30].

#### Stress

Saliva samples for cortisol measurements and stress scales will be performed at baseline and at the 6- and 13-month follow-up visits.

Saliva samples will be taken at 7 am, 11 am, 4 pm, and 11 pm during one workday. The participants are instructed to avoid high-intensity exercise on the day before as well as during the test day. They are also instructed not to eat, use nicotine, or brush their teeth one hour before the test. Premenopausal women are instructed to take the samples on the seventh day after the start of their menstruation. The participants will take the samples at home using Salivette® tubes. They are instructed to chew on the included swab for one minute or to keep the swab under their tongue for one and a half minutes. The swab is then put back into the tube and the lid is put on for storage. They will be instructed to keep the saliva samples in the refrigerator for up to one day before handing them over to the research team. The saliva samples will be analysed at the department of Clinical Chemistry, Umeå University hospital.

Self-reported stress during the past week will be measured using the Stress- and Energy scale (SE scale) [31]. The participants will complete the questionnaire at home. This scale consists of 12 adjectives of which 6 cover the dimensions of stress and 6 cover the dimension of energy. Answers are given on a 6-point scale (0–5) ranging from “not at all” to “extremely”.

#### Depression, anxiety

The participants’ feelings of depression and anxiety during the past week will be measured at baseline and at the 6- and 13-month follow-up visits using the HAD scale [21]. The participants will fill out the questionnaire at home.

#### Cognitive functions

A cognitive test battery covering functions including episodic memory, working memory, and executive functions will be administered at 0, 6, and 13 months. The tests will be performed at Umeå University during office hours. The total time for the cognitive tests will be approximately 45 min. The selected tests are a mixture of computerized tests and pen and paper tests. Below are descriptions of each test and the order of the tests.

##### Free recall, episodic memory [32]

In free recall, the participants will be presented with a list of 16 words on a computer screen at the rate of three seconds per item. When the list is completed, a free recall test will follow (maximum 2 min) where the participants will be asked to recall as many of the previously presented words as possible. The dependent variable will be the number of correctly recalled words.

##### N-back, executive function [33]

In n-back, the participants will be asked to indicate whether each number (1–9) in a list presented on a computer matches a number occurring one, two, or three numbers back. Accuracy and response time will be used as dependent measures.

##### Encoding, episodic memory (recognition)

In this test, the participants will be presented with a list of 30 words on a computer one at a time for three seconds per item. The task is to encode each word for a subsequent memory test (retrieval-recognition; see below).

##### Flanker test, executive function [34]

In the Eriksen flanker task, the participants will indicate the direction of the middle arrow in either congruent (>>>>>) or incongruent (> > <>>) stimuli presented on a computer by pressing a button as fast and as accurately as possible. Accuracy and response time will be used as dependent measures.

##### Backward digit span, working memory [35]

In Digit span, the participants will be asked to recall digits backwards. The dependent variable will be the longest correctly completed number sequence.

##### Trail making A + B, working memory and executive function [36]

In the trail making test (TMT), the participants will be shown circles containing letters and numbers. They will be asked to connect the circles containing numbers in numerical order (TMT part 2) and to alternate between numbers and letters according to numerical and alphabetical order (TMT part 4). This is a pen and paper test. A shifting cost will be calculated, i.e. the difference in time (seconds) taken to complete TMT part 4 as compared to TMT part 2.

##### Retrieval-recognition, episodic memory

In this test, a new list of words will be presented to the participants. The list contains the words from the encoding phase (see above) and the task is to indicate if the words have previously been presented or not. The dependent variable will be the number of correctly recognized items.

##### Digit symbol, processing speed [35]

In digit symbol, the participants will be required to draw symbols in empty boxes, associating them with numbers according to a coding key. The number of items completed in 90 s will be used as the outcome measure.

Brain-derived neurotrophic factor (BDNF) will be measured in plasma samples from baseline and at the 6- and 13-month follow-up visits. BDNF has previously been shown to correlate to neuronal plasticity, including effects on the hippocampal volume [37].

#### Functional Magnetic Resonance Imaging (fMRI)

Twenty subjects from each study group will be randomly selected for fMRI scanning at baseline and at the 13-month follow-up. This will be performed at the Centre for Functional Brain Imaging at the University hospital in Umeå, Sweden. The participants will be instructed to eat as usual before the measurement, but to refrain from nicotine and caffeine one hour before the test and from high-intensity exercise and alcohol for twenty-four hours before the test.

High-resolution T1 images will be acquired in order to examine potential effects on grey matter volume. Furthermore, blood oxygen level dependent (BOLD) T2* images will be acquired during a 10 min rest period in order to evaluate functional resting state networks, a measure of global brain function across various ages [38]. The last task during scanning will be the Eriksen flanker task to evaluate task-specific effects on functional brain response. In the Eriksen flanker task, participants will indicate the direction of the middle arrow in either congruent (>>>>>) or incongruent (> > <>>) stimuli by pressing MRI-adapted buttons as fast and as accurately as possible. Accuracy and response time will be used as dependent measures.

#### Interview

At short-term follow-up visits, studies testing the effects of treadmill workstations have found that participants are generally positive and enthusiastic about the treadmill and would use it if available [13, 39]. A recent study investigated facilitators and barriers regarding usability, safety, comfort, and productivity in five female office workers who used treadmill workstations for 6 months [40]. By conducting an interview study after the study period is over, i.e. after 13 months, we will investigate the participants’ experiences with and attitudes towards working on a treadmill workstation, and further assess barriers and facilitators. The interview results may help with the development and implementation of active workstations and in the construction of activity-enhancing workplaces in the future.

This qualitative interview study includes individual semi-structured interviews. Approximately 15 interviews are estimated to be needed. Participants from the intervention group, who started in April 2014, will firstly be asked to participate. If more interviews are needed after this, participants from the intervention group starting in October 2014 will also be invited to participate. The interviews will be performed either at the companies where the participant works or at the university, depending on what works best for the participant. The study will be conducted using grounded theory methodology with an emergent design. The data will be processed through open, axial and selective coding, with constant comparison of the emerging codes. Using this method, our aim is to develop a theoretical model based on the gathered data. The credibility of the results will be determined by triangulation, where three members of the research team will perform the analysis independently.

### Sample size

Sample size calculation was based on two previous long-term studies on treadmill workstations available at the time the study was planned. These long-term studies found a significantly increased time spent walking per day [15, 16] after installing treadmill workstations. Based on these studies and stratification according to BMI (25–30 kg/m^2^ and 30–40 kg/m^2^), a study with 30 participants per group would have 85 % power in finding a statistically significant difference in 30 min of walking per day (SD 60, 8 min) between the groups. To compensate for an estimated dropout rate of 30 %, 39 individuals per group will be needed. Thus, 80 participants in total will be recruited for the Inphact Treadmill-study.

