Occupation plays a major role in the daily amount of NEAT. The prevalence of jobs based on sedentary tasks in the US has continuously increased since the 1960’s, while more physically demanding jobs have decreased in prevalence [6]. Studies from Australia, Scotland, and Sweden have shown that office workers spend between 66-82 % of their work hours sedentary [7–10]. Furthermore, sedentary time seems to be higher on workdays compared to non-workdays [8, 10, 11] as well as during working hours compared to non-working hours on workdays [10]. Church et al. concluded that the drop in energy expenditure due to an occupational change from active to sedentary jobs is a main reason for the increase in overweight and obesity over the past decades [6]. Workplaces are important targets when it comes to reducing sedentary behaviour [6–8]. If we could find ways to decrease sedentary time in the workplace and replace it with LPA, increasing NEAT, health gains are likely to be gained.

A key element to make the environment in offices more activity-permissive may be the implementation of active workstations. This consists of treadmills or other devices, such as bicycles or stepping devices that the employees use while working as usual at their desk. A recent review concluded that treadmill workstations can have positive effects on sitting time, energy expenditure, and different health parameters such as hip and waist circumference, weight, body fat percentage, high density lipoprotein (HDL), low density lipoprotein (LDL), and total cholesterol [12]. However, earlier studies of treadmill workstations were either of rather short duration (up to 12 weeks) [13, 14], lacked a control-group [15, 16], or included a control group that was followed for a shorter time period than the intervention group [17]. Importantly, no randomized controlled trials (RCTs) have investigated the long-term impact of treadmill workstations on reducing sitting time during working hours [18].

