## Methods

### Trial design

The Inphact Treadmill study is a two-arm, randomized, controlled study. Participants will be individually randomized into either an intervention group or a control group with an allocation ratio of 1:1. The study will be conducted and reported in accordance with the CONSORT guidelines.

The Inphact Treadmill study is funded by Umeå University.

Ethical approval was granted by the Regional Ethical Review Board, Umeå, Sweden.

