### Statistical methods

Primary analyses will follow intention-to-treat principles. Changes over time between the two study arms and across the different data collection time points will be analysed using methods that account for within-subject dependencies, e.g. mixed models. The threshold for statistical significance will be set at *p* <0.05. Adjustments will be made for baseline characteristics and potential confounding variables, such as age and gender.

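### The stated 85 % power does not follow from the printed inputs: 30 per group, a 30-minute difference and an SD of 60.8 give about 47 %

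*Protocol article*

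**What the plan says.** The Sample size section of the protocol article bases its calculation on two earlier long-term treadmill-workstation studies and on stratification by BMI (25–30 and 30–40 kg/m²). It states that "a study with 30 participants per group would have 85 % power", and describes this as "power in finding a statistically significant difference in 30 min of walking per day (SD 60, 8 min) between the groups". It then allows for 30 % dropout, arrives at 39 per group, and rounds to 80 participants in total.

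The other inputs are elsewhere in the article. Trial design specifies individual randomisation "with an allocation ratio of 1:1". Statistical methods says that "The threshold for statistical significance will be set at *p* <0.05", without stating sidedness, and gives mixed models as an example of a method that handles within-subject dependence, with adjustment for baseline characteristics. Table 1 has walking time measured at baseline and at 2, 6, 10 and 13 months. Hypotheses names walking time, intervention against control, as the primary hypothesis.

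**The concern.** The paragraph prints a sample size, a between-group difference, an SD and a power. With the 5 % threshold, that is all a two-group calculation needs, so the four numbers should agree. They do not, and the gap is far larger than rounding or the placing of the decimal comma could explain.

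This paragraph is the article's only justification for the size of the trial, and it concerns the primary hypothesis. A reader who accepts 85 % would treat a null result on walking time as fairly strong evidence against a 30-minute effect. If the test were the simple two-group comparison that the paragraph describes, a true 30-minute effect would be missed slightly more often than found.

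**Working it through.** **Inputs**
- n = 30 per group and power 85 % (Sample size)
- difference δ = 30 min/day between the groups (Sample size)
- SD σ = 60.8 min, reading the printed comma as a decimal comma; 60 is tried as well (Sample size)
- 1:1 allocation (Trial design)
- α = 0.05 (Statistical methods); two-sided assumed, one-sided tried as well

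**Attempt to reproduce 85 %.** For a two-sample t test the standardised difference is δ/σ = 30/60.8 = 0.493. The standard error is σ√(2/n) = 60.8 × √(2/30) = 15.70 min, so the noncentrality is 30/15.70 = 1.911. The two-sided 5 % critical value on 58 degrees of freedom is 2.002. The expected test statistic therefore lies below the critical value, and power must be a little under one half.

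| Case | Power for 30 min |
|---|---|
| 30 per group, SD 60.8, two-sided | 46.8 % (normal approximation 48.0 %) |
| 30 per group, SD 60.8, one-sided | 59.6 % |
| 30 per group, SD 60, two-sided | 47.8 % |
| 28 per group (40 × 0.7), SD 60.8, two-sided | 44.2 % |
| 40 per group, no dropout, SD 60.8, two-sided | 58.7 % |
| Stated | 85 % |

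**What 85 % would need (two-sided 5 %)**
- At 30 min and SD 60.8: 75 per group (73 if the SD is 60).
- At 30 per group and SD 60.8: the detectable standardised difference is 0.787, so δ = 0.787 × 60.8 = 47.8 min.
- At 30 per group and 30 min: σ = 30/0.787 = 38.1 min.

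**Could BMI stratification explain it?** The residual variance would have to be (38.1/60.8)² = 0.393 of the total, so a two-level BMI factor would have to account for about 60 % of the variance in walking time. The article claims no such gain.

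**Could baseline adjustment or repeated measures explain it?** None of the following is stated in the article. Compound symmetry with correlation r and an effect constant over time are assumed.
- *One follow-up adjusted for baseline:* the variance factor is 1 − r². Setting it to 0.393 gives r = √0.607 = 0.78.
- *Mean of the four follow-ups adjusted for baseline:* the variance factor is (1 + 3r)/4 − r². The result depends on what 60.8 measures. If it is the SD of change, the SD of walking time is 60.8/√(2(1 − r)).

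| r | Factor | Power, 30 per group, if 60.8 is the SD of walking time | Power, 30 per group, if 60.8 is the SD of change |
|---|---|---|---|
| 0.3 | 0.385 | 85.7 % | 94.8 % |
| 0.5 | 0.375 | 86.6 % | 86.6 % |
| 0.7 | 0.285 | 94.1 % | 77.8 % |
| 0.8 | 0.210 | 98.4 % | 73.7 % |

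At 28 per group and r = 0.7 the last two columns become 92.5 % and 74.9 %. The averaged contrast can therefore fall on either side of 85 %, depending on two quantities that the article does not give.

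**The case against.** The strongest reply is that the planned analysis is not a two-sample t test. Walking is measured five times, and Statistical methods envisages a method for correlated data with baseline adjustment. For a baseline-adjusted mean of four follow-ups, power can be 85 % or more with 30 per group. A condensed article may also leave the assumed correlation to the full protocol.

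Most of this stands as a limit on the conclusion. A reader might infer that the trial has only 47 % power, and the documents do not support that. It does not rescue the paragraph, which mentions no correlation, number of measurements or averaged contrast. Mixed models appear only as an example, and no primary time point or average is fixed. A single-visit contrast such as month 13 would need a baseline correlation of about 0.78. The fault is that the printed numbers disagree with one another, which is different from leaving out a detail.

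A second tempting inference is that a one-arm, before–after calculation was carried over into a two-arm trial. The Background does say that the two source studies "lacked a control-group [15, 16"], and a two-sided one-sample test with these inputs happens to reach 85 % at n = 39. But an uncontrolled study also reports cross-sectional SDs, so the article does not show that 60.8 is a within-person SD. The figure 39 is simply 30 × 1.3, and the 85 % is attached to 30, where the one-sample test gives 74 % two-sided. This inference should not be drawn.

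**Conclusion.** The point holds in this form: 85 % power does not follow from the inputs printed beside it. Those inputs give about 47 % two-sided, and no standard two-group reading (one-sided, normal approximation, or SD 60) exceeds about 62 %. In sample-size terms, the inputs call for about 75 per group where the paragraph has 30.

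This rests on reading the SD as 60.8 and the comparison as two independent groups of 30 at the 5 % level, as the paragraph describes. It does not establish the power of the eventual mixed-model analysis, which cannot be determined without the contrast, the correlation and the meaning of the SD. The paragraph needs correcting because it is the trial's only size justification and concerns the primary outcome.

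**What to change.** Restate the paragraph: with 30 analysed per group and an SD of 60.8 min, a two-sided 5 % comparison at a single time point has about 47 % power for a 30-min difference and 85 % power for about 48 min.

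Claim a higher power only if it is recomputed for the repeated-measures contrast actually planned. In that case print the test, the sidedness, whether 60.8 is the SD of walking time or of its change, and the assumed correlation. If the calculation was done that way from the start, adding these inputs settles the matter.

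The contrast should not be chosen because it brings the figure back to 85 %. An average over all four follow-ups includes month 2, in a trial whose stated aim is long-term effect, and it reaches 85 % only under some readings of the SD.

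Recruitment is complete and no extra participants are needed. The cost is one reworded paragraph and a less favourable stated figure.

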### Randomization

After the baseline measurements, participants will be individually randomized by an external statistician into one of the two groups, with 40 participants per group. They will be stratified according to BMI (25–30 kg/m^2^ and 30–40 kg/m^2^).

For the fMRI-measurement, 20 of the eligible participants from each group will be randomly selected to participate.

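### The allowance for 30 % dropout is too small: keeping 30 per group needs 43 randomised, and the planned 40 leave 28.

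*Protocol article*

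**What the plan says.** The Sample size section of the protocol article gives the base requirement: "a study with 30 participants per group would have 85 % power". The target is a "difference in 30 min of walking per day (SD 60, 8 min) between the groups".

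It then adds the dropout allowance: "To compensate for an estimated dropout rate of 30 %, 39 individuals per group will be needed". The conclusion drawn is: "Thus, 80 participants in total will be recruited for the Inphact Treadmill-study".

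The Randomization section confirms the operative number, "with 40 participants per group", and the Trial design section gives the allocation as 1:1. The article describes no other allowance for dropout.

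**The concern.** The 30 per group is the number the plan wants left after losses, and 30 % is its own estimate of those losses over 13 months. The number to randomise must therefore still leave 30 once 30 % have gone. Neither 39 nor 40 does so.

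At stake is the sample-size justification for the primary outcome. A reader will take it that the trial keeps its stated power at the expected dropout. In the scenario the plan itself expects, the trial falls below its own target.

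**Working it through.** **Inputs**

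- Required per group after dropout: n = 30 (Sample size)
- Dropout: d = 0.30 (Sample size)
- Stated number after the allowance: 39 per group (Sample size)
- Planned: 80 in total, 40 per group (Sample size, Randomization)
- Difference 30 min/day; the SD is printed with a comma and a space and is read here as 60.8 min (Sample size)
- Significance level 0.05 (Statistical methods); the number of sides is not stated, and two-sided is assumed

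**Reproducing the plan's figure**

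n × (1 + d) = 30 × 1.30 = 39.0. This matches exactly. The article prints no formula, so the multiplier is inferred from the match.

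**Number needed**

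n / (1 − d) = 30 / 0.70 = 42.86, so 43 per group and 86 in total. Check: 43 × 0.70 = 30.1.

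**What the stated and planned numbers leave**

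| Randomised per group | Left at 30 % dropout | Highest dropout that still leaves 30 |
|---|---|---|
| 39 | 39 × 0.70 = 27.3 | 1 − 30/39 = 23.1 % |
| 40 | 40 × 0.70 = 28.0 | 1 − 30/40 = 25.0 % |
| 43 | 43 × 0.70 = 30.1 | 1 − 30/43 = 30.2 % |

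The shortfall in enrolment is 43 − 40 = 3 per group, or 86 − 80 = 6 in total. The shortfall in completers at 40 per group is 30 − 28 = 2 per group. The middle column does not depend on how the 39 was obtained.

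**Effect on power, taking the plan's 85 % at 30 per group as given**

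In the normal approximation, 85 % power corresponds to a standardised difference of 1.960 + 1.036 = 2.996. At 28 per group this becomes 2.996 × √(28/30) = 2.895, and power is Φ(2.895 − 1.960) = Φ(0.935) = 82.5 %. The noncentral-t version gives 82.4 %. The difference detectable with 85 % power rises from 30 to about 30 × √(30/28) = 31.1 min/day.

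**Effect on power, taking the printed difference and SD**

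With 30 min, SD 60.8 min and a two-sided t-test, power is 46.8 % at 30 per group and 44.2 % at 28. The gap between these values and 85 % concerns the base calculation and is a separate matter. On either basis the dropout step costs about 2.6 percentage points.

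**The case against.** The arithmetic itself is hard to dispute; the case on the other side is that it matters little. Four points can be made.

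- **The loss is small.** The trial randomises 40 per group, not 39, so it is two completers short per group. About 2.6 points of power is little beside the uncertainty in a dropout rate that is only an estimate. This stands, and it limits the weight of the finding.
- **Recruitment is finished.** The Trial status section says so, so the number cannot be changed on account of this point. This also stands; the remedy is a correction to the stated justification.
- **Completers are not the whole analysis set.** The Statistical methods section plans intention-to-treat analysis with methods such as mixed models, and Table 1 measures walking time at baseline, 2, 6, 10 and 13 months. Someone who leaves after a follow-up visit still contributes data, so a count of 28 per group probably understates the information available. This softens the consequence. However, the Sample size section makes no such argument: it sets 30 per group as the target and claims to protect it.
- **If the base power figure is wrong, missing 30 by two hardly matters.** It is true that the base calculation has the larger consequence, and the two effects should not be blended. The statement about dropout is still incorrect in its own right.

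**Conclusion.** The concern holds. At the plan's own 30 % dropout, 39 per group do not leave 30, and neither do the 40 actually planned. The correct figure is 43 per group, 86 in total. The planned 40 per group cover dropout up to 25 % and leave 28 at 30 %.

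The consequence is modest: power of about 82 % instead of 85 % if the plan's base figure is accepted, or about 44 % instead of 47 % on the printed difference and SD. Both pairs assume a two-sided 5 % comparison of two means; the second also assumes the SD reads 60.8 min. The head count rests only on the 30, the 30 % and the 40 printed in the article. That the slip came from multiplying by 1.3 is a likely inference, and the conclusion does not depend on it.

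**What to change.** Correct the dropout sentence in the Sample size section. It should say that 43 per group would be needed to keep 30 at 30 % dropout, and that the 40 per group randomised keep 30 at up to 25 % dropout and 28 at 30 %. Report power and detectable difference at 28 per group, once the base power calculation has been checked against the printed difference and SD. If the authors wish to rely on data from participants who leave early, they should say so and give the assumption.

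The cost is one corrected sentence and a slightly less favourable stated figure. Enrolment, randomisation and analysis stay as they are. Correcting 39 to 43 repairs the dropout step only and does not by itself secure 85 % power.
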